### Plans for collection, laboratory evaluation and storage of biological specimens for genetic or molecular analysis in this trial/future use {33}

Not applicable. No biological specimens will be collected, and no genetic or molecular analyses will be conducted in this trial.

## Statistical methods

### Statistical methods for primary and secondary outcomes {20a}

The primary analysis will follow the intention-to-treat (ITT) principle, including all randomized participants in their assigned groups regardless of intervention adherence. The primary outcome is maternal psychological distress (Kessler-6) at 12 months post-intervention (T2). The key secondary outcome is parent-reported child psychosocial wellbeing (Kiddy-KINDL^R^ Parent Report) at T2. To control the overall type I error rate across the primary and key secondary outcomes, we will use a hierarchical fixed-sequence testing procedure: K6 will be tested first at two-sided *α* = 0.05, and Kiddy-KINDLR will be formally tested at two-sided *α* = 0.05 only if the primary test is statistically significant [55]. For the primary and secondary outcomes, we will use linear mixed-effects models (LMM) with random intercepts for villages and participants. The primary estimand for hypothesis testing is the T2 outcome value (final value), with adjustment for the baseline (T0) value of the same outcome when measured at baseline. A pre-specified covariate-adjusted model will be run as a robustness check, additionally adjusting for maternal age and education, child age and sex, household size, and time in the settlement. Results will be presented as adjusted mean differences with 95% confidence intervals and as standardized mean differences (Hedges’ *g*). Outcomes measured at 3 months (T1) will be analyzed analogously as supportive time points to characterize trajectories.

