## Introduction

### Background and rationale {6a}

Mental disorders contribute substantially to the global burden of disease and disability [1]. War-exposed refugee populations are at exceptionally high risk of mental health disorders, including post-traumatic stress disorder, anxiety, and depression [2, 3]. Refugee mothers, in particular, face distinct challenges that compound this risk, such as exposure to gender-based violence, the psychological burden of caregiving in precarious conditions, and systemic barriers to accessing support [4].

A mother’s psychological state is a cornerstone of the caregiving environment that fosters child development. Positive maternal mental health supports nurturing parenting and promotes children’s development and wellbeing [5, 6]. Conversely, psychological distress can destabilize family dynamics and reduce caregiving quality, hindering children’s socio-emotional and cognitive development [7–9]. These effects are especially consequential during the preschool years (ages 3–5), a period of heightened neuroplasticity when the developing brain is highly sensitive to environmental inputs [10].

These psychological burdens are particularly acute in humanitarian contexts, where exposure to past trauma combines with ongoing adversity. Yet a major treatment gap persists due to the scarcity of scalable, evidence-based interventions [11]. Beyond symptom reduction, improving maternal mental health may also strengthen caregiving and family functioning, with downstream implications for young children’s psychosocial wellbeing. Recent consensus-based research priorities for mental health and psychosocial support (MHPSS) in humanitarian settings highlight the need to assess both short-term and long-term benefits of MHPSS interventions and to better understand intergenerational impacts of adversity [11]. These priorities motivate the present trial’s 12-month endpoint and the inclusion of child psychosocial wellbeing as a key outcome. If efficient interventions can produce sustained improvements in maternal mental health, they may yield a double benefit: promoting maternal wellbeing while simultaneously fostering positive child development.

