### Sample size {14}

We determined the required sample size using *PowerUp!* [54], focusing on the primary outcome of maternal psychological distress (Kessler-6) [17] at the 12-month follow-up. Calculations were based on a two-arm cluster-randomized design with equal allocation and equal expected cluster sizes.

Our objective is to achieve 90% statistical power to detect a minimal clinically important difference (MCID), defined as Cohen’s *d* = 0.20, for the primary outcome using a two-tailed significance level (*α*) of 0.05. The parent-reported Kiddy-KINDL^R^ at T2 is specified as a key secondary outcome and will be tested using a hierarchical fixed-sequence procedure: K6 will be tested first at *α* = 0.05, and Kiddy-KINDL^R^ will be formally tested at *α* = 0.05 only if the primary test is statistically significant. This approach controls the overall Type I error rate across the primary and key secondary outcomes without requiring alpha adjustment of the individual tests [55]. While modest, an effect size of this magnitude (*d* = 0.20) is meaningful for a low-intensity, scalable intervention delivered by lay facilitators. In high-burden humanitarian settings, even small average improvements in psychological wellbeing can translate into substantial population-level benefits and policy relevance [56].

For the power calculation, we used an intra-cluster correlation coefficient (ICC) of 0.012, based on the values observed in the earlier SH+ cluster-RCT in the same setting and population [14]. The SH+ intervention is designed for delivery in groups of up to 30 individuals. To account for potential attrition over the 12-month study period, we conservatively assume a 20% dropout rate. Consequently, we plan to recruit 30 mother–child dyads per cluster, with an expected 24 analyzed per cluster at endline. Based on these parameters (power = 0.90, *α* = 0.05, *d* = 0.20, ICC = 0.012, *m* = 24 analyzed per cluster), *PowerUp!* indicates that 24 clusters (12 per arm) are required. This yields a total target sample of 720 mother–child dyads across 24 villages within Rhino Refugee Settlement.

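### Both covariate lists for the child and parenting outcomes omit baseline maternal K6; the models are valid without it, but adding it before 12-month data are seen is a cheap, modest improvement

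*Protocol article*

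**What the plan says.** Section {20a} of the Protocol article specifies linear mixed models for the T2 value, "with adjustment for the baseline (T0) value of the same outcome when measured at baseline". The robustness model goes further by "additionally adjusting for maternal age and education, child age and sex, household size, and time in the settlement". For the key secondary outcome (H2, parent-reported Kiddy-KINDL) the main model therefore carries baseline Kiddy-KINDL, and the robustness model adds six sociodemographic variables. Baseline K6 is in neither. The same holds for PSC-17, child self-report and the parenting scales.

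Other sections bear on this:
- Eligibility {10} and Outcomes {12}: K6 is an entry criterion (score of 5 or more) and a T0 outcome, so every enrolled mother should have it.
- Implementation {16c}: baseline data are collected before villages are allocated.
- Background {6a}: "psychological distress can destabilize family dynamics and reduce caregiving quality", with consequences for the child's development.
- Section {20b}: baseline maternal distress enters exploratory interaction models only.
- Outcomes {12}: a subset of the baseline variables will be controlled for, with a pointer to {20a} for which ones.

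**The concern.** The robustness list has room for household size and time in the settlement but not for the baseline variable on which the trial's theory of change rests. The mother also rates the key secondary outcome, so her distress could affect both the child's state and the score she gives.

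Three things are at stake, all modest:
- **Chance imbalance.** Only 24 villages are allocated, by a draw of shuffled envelopes with no stratification described ({16a}, {16c}). The arms can differ by chance in baseline K6, and neither listed child model adjusts for that directly.
- **Missing data.** Section {20c} relies on maximum likelihood under missing-at-random, and section {14} allows for 20% dropout. Missing-at-random is conditional on what the model contains. If more distressed mothers are lost more often, which is plausible but not documented, having K6 in the model makes the assumption easier to defend.
- **Precision.** If baseline K6 predicts T2 Kiddy-KINDL beyond baseline Kiddy-KINDL, the H2 test gains a little.

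Because K6 is measured before allocation, adjusting for its baseline value does not condition on a mediator.

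**Working it through.** **Inputs from the protocol ({14}).** 24 clusters, 12 per arm; 30 recruited and 24 analysed per cluster; two-sided alpha 0.05; d = 0.20; and "we used an intra-cluster correlation coefficient (ICC) of 0.012". That ICC is for K6. None is given for Kiddy-KINDL, so using 0.012 for it is an assumption.

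**The plan's own figure.** With no covariates, SE = sqrt(ICC/(0.25J) + (1−ICC)/(0.25Jm)) = sqrt(0.012/6 + 0.988/144) = 0.0941 SD. On a t test with 22 df, power at d = 0.20 is 53%, not the stated 90%. About 58 clusters would be needed. This is a separate and much larger matter that a K6 covariate cannot repair. It is noted here because it sets the starting level of power.

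**H2 before the change.** Baseline Kiddy-KINDL scales the SE by sqrt(1−R²). At an assumed R² of 0.16 the SE is 0.0863 and power is 60%. At an assumed R² of 0.25 (baseline–endline correlation 0.5) the SE is 0.0815 and power is 65.0%.

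**Adding baseline K6.** With partial correlation r beyond baseline Kiddy-KINDL, the SE is multiplied by sqrt(1−r²). Starting from R² = 0.25:

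| Assumed partial r | Fall in SE | Equivalent extra participants | Power at d = 0.20 |
|---|---|---|---|
| 0 | 0% | 0% | 65.0% |
| 0.05 | 0.1% | 0.3% | 65.1% |
| 0.10 | 0.5% | 1.0% | 65.4% |
| 0.20 | 2.0% | 4.2% | 66.8% |
| 0.30 | 4.6% | 9.9% | 69.1% |

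Charging one cluster-level degree of freedom costs about 0.2 percentage points of power.

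**Chance imbalance.** With 30 per village, the SD of the arm difference in baseline K6 is sqrt(4(1 + 29×0.012)/720) = 0.087 SD, so 95% of draws fall within 1.96 × 0.0865 = ±0.17 SD. At an assumed conditional slope of 0.1 to 0.3, an imbalance at that edge moves the child contrast by 0.017 to 0.051 SD, or about 8% to 25% of 0.20. An average draw is smaller: 0.8 × 0.0865 = 0.07 SD, which at a slope of 0.2 gives 0.014 SD, or 7% of 0.20 and about one-sixth of the SE of 0.0815.

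**Simulation check.** 24 clusters of 24, 4,000 runs per scenario, no true effect, baseline Kiddy-KINDL slope 0.5, correlation of −0.3 between the two baselines:

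| K6 slope | Empirical SE without K6 | With K6 |
|---|---|---|
| 0 | 0.0821 | 0.0822 |
| −0.1 | 0.0787 | 0.0785 |
| −0.2 | 0.0767 | 0.0747 |
| −0.3 | 0.0767 | 0.0717 |

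Both estimators were centred on zero in every scenario. The last row falls by 6.5%, more than the 4.6% above, because a slope is not a partial correlation: with residual variance 1 − (0.25 + 0.09 + 0.09) = 0.57, a slope of −0.3 gives partial r² = 0.0819/(0.57 + 0.0819) = 0.126, so |r| is about 0.35.

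**The case against.** The strongest reply is that nothing here is an error. Section {20a} names a valid confirmatory model and a prespecified robustness model, allocation is randomised, and almost any covariate list could be longer. That stands. A reader might infer that the H2 comparison is biased or confounded because K6 is left out. The documents do not support that: chance imbalance is already covered by the confidence interval, and the simulation shows no bias.

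A reader might also infer that adding K6 removes imbalance and is certain to gain precision. Neither follows. It adjusts for imbalance in K6 only. The gain depends on a partial correlation the documents do not give; baseline Kiddy-KINDL is rated by the same mother and may carry much of the same signal, and K6 is range-restricted by the entry cut-off. The shifts above also multiply a conditional slope by the full K6 imbalance. With baseline Kiddy-KINDL already in the model, only the part not explained by it counts, which is smaller by sqrt(1−ρ²), or 0.95 at a correlation of 0.3 between the two baselines. The Introduction itself calls the evidence on child benefits mixed.

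Other points stand in part. The {20b} interaction models would normally carry a K6 main effect, but they are exploratory and name no outcomes. The multiple imputation in {20c} could use K6 as an auxiliary variable; its model is not shown. Section {14} mentions cluster-level covariates without naming them, and {20a} lists none. That mismatch should be reconciled, but it does not put individual K6 into the child models. Child age and sex are already in the robustness model, so moving them into the confirmatory model is optional.

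**Conclusion.** The point holds as a minor improvement. Baseline K6 is absent from both covariate lists in {20a} for the child and parenting outcomes, although it is available on every mother and central to the stated rationale. The current models are valid and, under complete data, unbiased.

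The expected benefit for H2 is a fall in SE of 0.1% to 2% at partial r of 0.05 to 0.20, and 4.6% at 0.30, which takes power from 65.0% to at most 69.1% when baseline R² is 0.25. It may be nil. Protection against a K6 imbalance at the 95% edge is worth 0.017 to 0.051 SD at slopes of 0.1 to 0.3. The partial correlations, slopes, baseline R² and the Kiddy-KINDL ICC are all assumptions. The missing-data benefit is qualitative and depends on dropout being related to distress.

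**What to change.** By a documented amendment before any T2 data are seen, add baseline K6 as an individual-level covariate to the Kiddy-KINDL model in {20a} and to the models for PSC-17, child self-report and parenting. At minimum, add it to the robustness covariate list. Keep the own-baseline-only model as a sensitivity analysis. Moving child age and sex into the confirmatory model is optional.

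The cost is one more coefficient with about 576 analysed dyads (24 × 24), and no new data collection. Baseline collection is complete, so the change counts as an analysis-plan amendment to be notified under section {25}. The final 12-month assessments are expected to be completed in February 2027. Adding K6 later, in response to an imbalance already seen alongside T2 results, would be post hoc.

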### Interim analyses {21b}

No interim analyses for efficacy or futility are planned.

### Methods for additional analyses (e.g., subgroup analyses) {20b}

Exploratory subgroup analyses will be conducted to assess whether treatment effects vary by baseline maternal psychological distress, trauma exposure, and parenting practices. Effect moderation will be examined by including interaction terms (intervention × moderator) within the LMM framework.

### Methods in analysis to handle protocol non-adherence and any statistical methods to handle missing data {20c}

A per-protocol analysis will be conducted as a sensitivity analysis, including only participants who demonstrate adequate adherence to the intervention protocol. Missing data will be handled using maximum-likelihood estimation within the mixed-effects models, which is valid under the missing-at-random (MAR) assumption. If > 10% of observations are missing at T2, we will perform multiple imputation as a sensitivity analysis.

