#### Enhanced Usual Care (EUC)

All enrolled participants (mothers) will receive EUC, which consists of a single 15-min psychoeducation session delivered individually by a trained research assistant under the supervision of a clinical psychologist from our implementation partner, *vivo international*. The session is guided by a predetermined script, focusing on the locally salient concept of “overthinking” [22] and introducing brief, practical self-management techniques. Following the session, participants are provided with standardized information about available mental health resources within Rhino Refugee Settlement, including services provided by UNHCR partner organizations and a network of community-based health workers trained to offer basic psychosocial support. EUC is delivered to all participants after the baseline assessment; for those in the intervention arm, it precedes the start of SH+.

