#### Self-Help Plus (SH+)

Participants in the intervention arm will additionally receive Self-Help Plus (SH+), a World Health Organization (WHO) brief, low-intensity intervention designed for stress management in communities affected by adversity [12, 13]. SH+ is based on Acceptance and Commitment Therapy (ACT) and is delivered in a group-based format (up to 30 participants) over five weekly sessions, each lasting approximately 2 h.

The core content is delivered via pre-recorded audio material (using the Juba Arabic adaptation), which is integrated with individual exercises and guided group discussions. Participants also receive an illustrated, low-literacy self-help book to review strategies and practice skills between sessions. This multimedia format, guided by a facilitator manual, is designed to enhance fidelity and minimize extensive training demands, making it suitable for scalable delivery in low-resource settings.

Sessions are co-facilitated by pairs of trained local lay-providers who reside in the settlement, have completed at least secondary education, and are proficient in both Juba Arabic and English. The training and supervision of these facilitators are led by experienced mental health specialists from *vivo international Uganda*. These specialists first completed a comprehensive Training of Trainers (ToT) conducted by the research team using WHO materials and guidelines. The ToT equipped them to deliver the SH+ training, conduct fidelity assessments, provide supervision, and manage referral pathways. Following this, the *vivo* specialists provide the facilitators with 5 days of specialized SH+ training and a 3-day supervised, hands-on pilot with test participants. Ongoing weekly supervision from these specialists includes a review of session checklists, feedback on delivery, and guidance on managing group dynamics to ensure fidelity to the SH+ model.

SH+ materials have been professionally translated and culturally adapted into Juba Arabic following established best practices [26], and are publicly available on the WHO website [27].

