### Criteria for discontinuing or modifying allocated interventions {11b}

Participants are free to withdraw from the study interventions at any time upon their request without providing a reason. The intervention facilitators or the clinical supervisor may also recommend withdrawal for a participant if they determine that continued participation is not in the participant’s best interest. Withdrawal will not affect access to any services or benefits available in the settlement.

Specific criteria for discontinuation from the intervention include the identification of imminent risk of suicide or harm to self/others, or the emergence of severe, acute psychiatric symptoms (e.g., psychosis or manic episodes) that require immediate, specialized care beyond the scope of this intervention. In such cases, the participant will be immediately referred to the appropriate mental health services within the settlement, and their participation in the intervention will be discontinued. Discontinuation from the intervention does not imply withdrawal from the study; where safe and consented, participants will be followed for outcome assessments in line with the intention-to-treat approach.

This protocol does not specify conditions for modifying the allocated interventions, as both the EUC and SH+ interventions are standardized and delivered according to a manualized protocol to ensure fidelity. No therapeutic content modifications are permitted; facilitators may make brief, culturally appropriate clarifications to enhance comprehension without altering core content or procedures. All instances of participant withdrawal or discontinuation from the intervention will be documented and any safety-related referrals will be reported in accordance with the trial’s adverse-event procedures.

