### Participant timeline {13}

The SPIRIT participant flow diagram is shown in Fig. 2. Baseline data will be collected immediately after participants complete screening, provide informed consent, and are enrolled in the study. All participants will then receive a single session of Enhanced Usual Care (EUC) before randomization. Those assigned to the intervention arm will then participate in the Self-Help Plus (SH+) program, which consists of five weekly group sessions. Follow-up assessments will be conducted at 3 and 12 months post-intervention.

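### The per-protocol sensitivity analysis filters essentially only the SH+ arm, so it loses the randomised comparison and cannot serve as a robustness check of the primary result

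*Protocol article*

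**What the plan says.** The section on non-adherence and missing data {20c} plans one adherence analysis: "A per-protocol analysis will be conducted as a sensitivity analysis, including only participants who demonstrate adequate adherence to the intervention protocol". It does not say what counts as adequate, or how the criterion applies in each arm.

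Four other parts of the protocol article determine what that restriction does:

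- **EUC content.** The EUC section describes an intervention for all enrolled mothers "which consists of a single 15-min psychoeducation session delivered individually by a trained research assistant".
- **EUC timing.** Participant timeline {13}: "All participants will then receive a single session of Enhanced Usual Care (EUC) before randomization". Implementation {16c} also places enrolment and baseline assessment before cluster allocation.
- **SH+.** It goes to the intervention arm only and is delivered "over five weekly sessions, each lasting approximately 2 h".
- **Leaving SH+.** Under {11b} a mother may stop whenever she wishes, and the listed grounds for discontinuation include "the emergence of severe, acute psychiatric symptoms (e.g., psychosis or manic episodes) that require immediate, specialized care".

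The primary analysis is intention-to-treat, "including all randomized participants in their assigned groups regardless of intervention adherence" (section {20a}). The article describes no adherence analysis that keeps the randomised groups intact.

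**The concern.** A sensitivity analysis should put the primary question again under different assumptions. This one changes the population, and in effect changes it in one arm only. Mothers who miss SH+ sessions are dropped, while their counterparts in EUC villages, who would have missed sessions had they been offered, stay in. Attendance may well go with distress, mobility or workload, which may also predict K6 at 12 months.

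Agreement with intention-to-treat would then not demonstrate robustness. Disagreement could not be interpreted, because the effect of attending and the selection of attenders are mixed together. What is at stake is how a supplementary table is read. The confirmatory test does not depend on it.

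**Working it through.** The plan gives no figure for this analysis, so there is none to reproduce. The planned effect of d = 0.20 (Sample size {14}) serves only as a yardstick.

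**Step 1: where can non-adherence arise?**

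- *EUC.* It is complete before allocation. A mother who missed it did so before any arm was known, so excluding such mothers would be balanced in expectation.
- *Other psychosocial programmes.* Under {11d}, joining another intervention trial after randomisation is not a protocol deviation, so it gives no ground for exclusion.
- *SH+.* Five sessions after allocation, in one arm. This is the only remaining component.

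The restriction therefore acts essentially on the SH+ arm.

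**Step 2: the bias.** Let *p* be the adherent share of SH+ mothers. Let *g* be the difference between attenders and non-attenders in the outcome they would have had without SH+, after covariate adjustment. Then

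mean(all) = *p* × mean(attenders) + (1 − *p*) × mean(non-attenders),

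so mean(attenders) − mean(all) = (1 − *p*) × *g*.

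By randomisation, the EUC arm estimates the mean for all mothers without SH+. The per-protocol contrast therefore estimates the effect among attenders plus (1 − *p*) × *g*.

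**Step 3: numbers.** The documents give neither *p* nor *g*; both are assumed. Bias in SD:

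| Adherent share | g = 0.1 | g = 0.2 | g = 0.3 | g = 0.4 |
|---|---|---|---|---|
| 90% | 0.01 | 0.02 | 0.03 | 0.04 |
| 70% | 0.03 | 0.06 | 0.09 | 0.12 |
| 50% | 0.05 | 0.10 | 0.15 | 0.20 |

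The bias is zero when *g* = 0, and it changes sign with *g*.

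**Step 4: cross-check by another model.** Let attendance be a threshold on a normal variable with correlation *r* to the outcome. The bias is then *r* × φ(z)/*p*, where z is the standard normal cut-off exceeded with probability *p* and φ the normal density. For *p* = 0.7 and *r* = 0.2 this is 0.099 SD. The implied gap is 0.099/0.3 = 0.33 SD, in line with the 70% row.

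A simulation used 24 clusters of 24, ICC 0.012, no true effect, 6,000 runs per setting and a t-test on cluster means. Rejection rates at a nominal 5% were:

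| Adherent share, r | Per-protocol | Intention-to-treat |
|---|---|---|
| 90%, 0.1 | 5.2% | 5.1% |
| 70%, 0.2 | 16.2% | 5.1% |
| 60%, 0.3 | 42.9% | 5.5% |

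This test has no baseline adjustment. The planned model would probably leave a smaller correlation, so the per-protocol rates show the mechanism and do not forecast this trial.

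**Step 5: the alternative.** Suppose no EUC mother is exposed to SH+ and allocation has no effect on non-attenders. The complier-average effect is then the intention-to-treat effect divided by the exposed share. At 70% exposed, an intention-to-treat effect of 0.20 corresponds to 0.20/0.7 = 0.29. The interval widens by about the same factor: 1/0.9 = 1.11, 1/0.7 = 1.43 and 1/0.5 = 2.0 at 90%, 70% and 50% exposed.

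**The case against.** The case for the plan has real force.

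**Intention-to-treat is primary and the fixed-sequence test ignores this table.** This stands, and it limits the point to a cheap improvement.

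**The one-arm filter is inferred.** The criterion is undefined in a condensed article, and an analysis plan that is not shown could also exclude EUC mothers exposed to SH+. The passage in {11d} concerns other trials, not SH+ exposure. This stands as a caution, so the wording here is that exclusions fall essentially on the SH+ arm. It does not rescue the method, because moving the attendance threshold does not make a filter on SH+ attendance act on both arms. A missing threshold is not the point.

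**The planned models adjust for baseline.** This stands. If the same models are used, only the gap left after baseline K6 adjustment counts, and the covariate-adjusted model may shrink it further. If attendance were unrelated to outcome given those covariates, the analysis would be unbiased. That is a strong assumption, and deterioration after randomisation is one reason it could fail.

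**The remedy has assumptions too.** This stands. SH+ is delivered to groups within villages, so non-attenders could be affected by what attenders bring home. A complier effect is also close to a rescaled intention-to-treat estimate and adds little independent evidence of robustness.

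A reader might go further and infer that the analysis must flatter SH+. The documents do not support this. Discontinuation for acute symptoms points that way, but no frequency is given. Mothers in greater distress might attend more, and those who feel better or are working might skip sessions, which would reverse the sign.

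**Conclusion.** The point holds in limited form. As written, the per-protocol analysis excludes mothers essentially from the SH+ arm, loses the randomised comparison, and should not be presented as a robustness check of the primary result. This rests on EUC being completed before allocation and on SH+ being the only later component, both of which the protocol article states.

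The bias is (1 − adherent share) × the residual prognostic gap. The range of 0.01–0.20 SD rests wholly on assumed adherence of 50–90% and assumed residual gaps of 0.1–0.4 SD. No single cell of that table should be quoted as the expected bias. The direction is open. The primary test and the fixed-sequence procedure are unaffected.

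**What to change.** Replace the per-protocol analysis with a complier-average causal effect:

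- Use two-stage (instrumental-variable) estimation with randomised arm as instrument.
- Define exposure as at least one SH+ session attended.
- Adjust for the baseline outcome and account for clustering by village.
- State the assumptions: allocation has no effect on mothers who attend no session, which spillover within villages could violate, and SH+ exposure in EUC villages is negligible.
- If a version based on number of sessions is added, state that it also assumes a linear dose effect.

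If the per-protocol table is kept, label it descriptive and do not call it a sensitivity analysis of the primary result.

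The cost is a few lines in the analysis plan. The analysis uses the SH+ attendance record that the per-protocol analysis would need anyway. The price is a wider interval than intention-to-treat gives. Trial status expects the 12-month assessments to finish in February 2027, so the change can be fixed before those results are analysed.
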